## Abstract

**Background:**

Nowadays, stabilization splints for the management of bruxism and temporomandibular disorders (TMD) can be produced utilizing a digital workflow comprising a digital impression of the teeth, digital splint design, and computer-aided manufacturing of the splints. The latter is usually a milling process, however, more recently 3D printing gained popularity due to its better cost and time efficiency. It remains unknown whether 3D printed stabilization splints are inferior to milled splints regarding clinical outcomes.

**Methods:**

This clinical trial assesses the non-inferiority of 3D printed occlusal splints compared to milled occlusal splints in a monocentric prospective randomized single-blinded crossover trial with two cohorts. One cohort includes 20 participants with bruxism, the other 20 participants with pain-related TMD, i.e., myalgia, myofascial pain, or arthralgia of the jaw muscles/the temporomandibular joint(s) diagnosed according to the Diagnostic Criteria for Temporomandibular Disorders (DC/TMD). Michigan-type stabilization splints are fabricated in a digital workflow by milling or 3D printing using CE-marked materials within their intended purpose. The participants wear a milled and a 3D printed splint in a randomized order for 3 months each, with follow-up visits after 2 weeks and 3 months. Investigated outcome parameters are oral health-related quality of life (OHRQoL) evaluated by the Oral Health Impact Profile (OHIP-G14), participant satisfaction as rated on a visual analog scale, therapeutic efficacy, and technical result of the splints. In this context, therapeutic efficacy means antagonist wear and—in the TMD group—reduction of pain/disability assessed by the Graded Chronic Pain Scale (GCPS v2.0) and clinical assessment following the DC/TMD standard, while technical outcome measures splint fit, wear and fracture rate.

**Discussion:**

The trial will provide important information on the clinical outcome of 3D printed stabilization splints in comparison to milled splints and will, therefore, enable an evidence-based decision in favor of or against a manufacturing process. This, in turn, will guarantee for a maximum of the patient’s OHRQoL during splint therapy, therapeutic efficacy, and longevity of the splints.

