
### Objectives {7}

Therefore, the objective of this clinical trial is to analyze whether the clinical outcome of 3D printed stabilization splints is inferior compared to milled stabilization splints in terms of patients´ OHRQoL and satisfaction with the splints, therapeutic efficacy, and technical outcome. These parameters will be investigated in both—a cohort comprising participants with bruxism and a cohort with participants suffering from pain-related TMD—over a period of 6 months. The null hypothesis states that novel 3D printed stabilization splints for use in bruxism or TMJ and/or jaw muscle pain are not inferior to milled stabilization splints with regard to the aforementioned parameters.

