### Trial design {8}

The clinical trial to assess the non-inferiority of 3D printed stabilization splints compared to milled stabilization splints is designed as a monocentric prospective randomized single-blinded crossover trial with two cohorts. According to the indication spectrum of stabilization splints, one cohort comprises 20 participants with bruxism whereas the other arm is formed by 20 participants with pain-related TMD. Only CE-labeled materials are used within their intended purpose for the fabrication of milled and 3D printed splints. In both cohorts, the treatment sequence, meaning that participants either receive a milled splint first and then a 3D printed splint or vice versa is randomized and allocated at a ratio of 1:1. The 3D printed and milled stabilization splints are each worn for 3 months in an order that is blinded to the participants.

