### Sample size {14}

The sample size was calculated based on results reported for the OHIP-G14. According to the results of Alajbeg et al. [29], an OHIP-G14 score of 25.29 (SD 12.38) can be assumed for TMD patients. If the non-inferiority margin is set at 5 and a standard deviation of the differences of 10 is assumed, 38 participants are required for the trial with a two-sided paired t-test and a power of 90% on a 5% significance level. As both cohorts can be analyzed together for the primary outcome parameter OHIP-G14, the target number of cases is set at 20 participants per cohort, resulting in 40 participants in total.

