## Statistical methods

### Statistical methods for primary and secondary outcomes {20a}

Absolute and relative frequencies are calculated for binary or categorical variables. For continuous data, the median, mean and standard deviation are specified. In addition, 95% confidence intervals are calculated. The calculations are performed per group (milled and 3D printed) and per cohort (bruxism and TMD). Cross-over effects are examined in all analyses. For the primary outcome parameter OHIP-G14, the group differences are estimated and tested using a linear regression model with corresponding two-sided 95% confidence intervals. The model will include the difference in OHIP-G14 values (milled vs. 3D printed) as a dependent variable and the sequence of the splints and the cohort (bruxism and TMD) as independent variables.

The one-sided test for non-inferiority of 3D printed versus milled splints at the 2.5% significance level is based on the two-sided 95% confidence interval of the linear regression model. The null hypothesis is rejected if the lower limit of the confidence interval for the difference (conventionally milled vs. 3D printed) is above − 5. The same applies to secondary outcomes, namely volume loss of the splint/opposing dentition, pain reduction, jaw mobility, and splint fracture rates.

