For the diagnosis of TMD, the DC/TMD, primarily established as RDC/TMD in 1992 and updated in 2014, can be regarded as the standard assessment and diagnostic tool [30]. For this reason, participants are examined and diagnosed following the guidelines of the DC/TMD in the present trial. Only pain-related TMDs are included in the trial as these conditions—but not pain-free intra-articular TMD—can be effectively managed by stabilization splints. These diagnoses are also used to discern the bruxism cohort, in which such a diagnosis led to exclusion. As an additional tool to assess trial eligibility, the GCPS is applied in the TMD cohort as a short, reliable, and valid instrument [38] for which a correlation with splint treatment effects was established [39]. Patients with GCPS grade III and IV are excluded since these scores point to high pain and moderate to severe disability that in most cases cannot be sufficiently alleviated by splint treatment and instead require multimodal pain therapy [39].

The bruxism and TMD cohort are then investigated for differences in OHRQoL and participant satisfaction with the splints in relation to their fabrication mode. OHRQoL was chosen as the primary outcome parameter, as OHRQoL with the splints determines participant compliance and thus the use of the splint, which consequently has an impact on the therapeutic efficacy and the technical outcome of the splint. The assessment of OHRQoL, therefore, forms the base for the future selection of treatment options enabling a maximum of treatment comfort and benefit for the patients [40]. For assessment of OHRQoL, the OHIP-G14 is used, which is an established questionnaire focusing on the evaluation of oral function, orofacial pain, orofacial appearance, and psychological impact [41–44]. To further integrate questions that specifically focus on participant satisfaction with the splints, participants are asked to rate wear comfort and retention of the splints on a Visual Analog Scale (VAS). Therapeutic efficacy and technical outcome are evaluated since these parameters determine clinical applicability as well as the service life of the splints and are therefore—in conjunction with OHRQoL—important measurements for the cost and benefit ratio. Especially for the GCPS, it was shown that it allows monitoring of even small changes in TMD symptoms [20] turning it into a sensitive instrument to validate therapeutic efficacy.

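### The OHIP-G14 non-inferiority limit of −5 is also applied to splint fracture rates, where it can be met with little or no evidence; 40 splints per type worn for 3 months do not support the abstract's longevity claim

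*Protocol article*

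**What the plan says.** All references are to the protocol article.

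- **Exposure.** Under Trial design {8}: "The 3D printed and milled stabilization splints are each worn for 3 months". The visit schedule under Intervention description {11a} puts the last check of each splint at 11 to 13 weeks after it is fitted. Objectives {7} describes the investigation as running "over a period of 6 months".
- **Number of splints.** Under Sample size {14}: "the target number of cases is set at 20 participants per cohort, resulting in 40 participants in total". Everyone crosses over, so there are at most 40 splints of each type. That number was derived for OHIP-G14 only.
- **Technical outcomes.** Outcomes {12} measures splint wear as volume loss from fitting to the 3-month control. Fracture is checked at control visits and reported as a percentage per splint type.
- **Decision rule.** Statistical methods {20a} sets the rule for OHIP-G14 in a regression on the within-person difference: non-inferiority if the lower limit of the two-sided 95% interval (milled versus printed) is above −5. The closing sentence extends this to the secondary outcomes, ending with "pain reduction, jaw mobility, and splint fracture rates". No separate margin for fracture is given.
- **Claim.** The Discussion part of the abstract says the resulting decision will guarantee a maximum of quality of life during splint therapy, "therapeutic efficacy, and longevity of the splints".

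**The concern.** A margin of 5 points belongs to a questionnaire scored from 0 to 56 and has no meaning on the scale of a fracture proportion. Fracture is also an outcome for which 40 short exposures per type may produce very few events, and in that situation an interval based on the observed variance collapses. The rule could then return a formal finding of non-inferiority on fracture that carries almost no information.

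The abstract supplies the interpretation such a finding would invite: that the trial tells dentists which splint lasts. The main Discussion also links the technical outcomes to the cost and benefit ratio. The one limit on applicability that it states concerns other printed materials and does not mention the short wear time.

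**Working it through.** **Inputs.** 40 participants, hence at most 40 splints per type (Sample size {14}); 3 months of wear each (Trial design {8}); limit −5 on milled minus printed (Statistical methods {20a}). The article gives no expected fracture rate and no sample size for fracture, so there is no planned figure to reproduce. Every fracture risk used below is an assumption.

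**Exposure.** 40 × 3/12 = 10 splint-years per type, none of it beyond about 13 weeks for any one splint.

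**Reading 1: fracture coded 0/1.** Each within-person difference is −1, 0 or 1.
- Worst case: all 40 printed splints break and no milled splint does. The difference is −1 with no variance, the lower limit is −1, and −1 > −5. The rule is met.
- General bound for the plain paired interval: with mean m, the standard error is at most √((1 − m²)/39). The lower limit is therefore at least m − 2.023 × √((1 − m²)/39) = m − 0.324 × √(1 − m²), whose minimum is −√(1 + 0.324²) = −1.05. No data set comes near −5.

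**Reading 2: −5 as percentage points.** Plain paired interval, covariates ignored, t(39) = 2.023.
- 0 printed and 0 milled fractures: difference 0, standard error 0, interval from 0 to 0. The rule is met.
- 1 printed and 0 milled: difference −1/40 = −2.5 points, standard error 2.5 points, lower limit −2.5 − 2.023 × 2.5 = −7.6. Not met. Adding balanced sequence and cohort terms (37 degrees of freedom, t = 2.026) also gives −7.6.
- If no milled splint breaks, the verdict thus turns on whether a single printed splint breaks.

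**What 0 of 40 shows.** Exact two-sided 95% upper limit = 1 − 0.025^(1/n).
- n = 40: 1 − 0.025^(1/40) = 8.8% per 3 months, which is beyond a 5-point margin.
- Over 12 months, assuming a constant hazard: 1 − (1 − 0.088)^4 = 31%.
- n = 20 (one cohort; the article plans summaries by cohort): 1 − 0.025^(1/20) = 16.8% per 3 months.

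**How often no printed splint would break, by assumed true 3-month risk: (1 − p)^40.**

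| Assumed risk | No fracture in 40 |
|---|---|
| 1% | 67% |
| 2% | 45% |
| 3% | 30% |
| 5% | 13% |
| 10% | 1.5% |

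**Error rate under reading 2.** Assume printed splints break at 5% and milled splints never do, so the truth lies exactly on the limit. Non-inferiority is then declared when no printed splint breaks, with probability 0.95^40 = 13%, against the nominal one-sided 2.5%.

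**The case against.** Several counter-arguments deserve a fair hearing.

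- **The unsuitable margin is a problem of scale, not of duration.** This is right as far as it goes: the 0/1 reading would fail with years of wear too. But short exposure and few splints make the zero-variance case plausible, and both problems meet in the same fracture conclusion.
- **The extension may mean only the method, not the number −5.** The sentence can be read that way. Fracture then has no stated margin, and an interval from 0 to 0 clears any negative limit, so the degenerate case remains.
- **Part of the remedy is already planned.** Statistical methods {20a} foresees frequencies and 95% intervals per splint group and cohort. This stands. What is missing is an exact interval and the removal of the formal decision.
- **Zero fractures is not a given.** This stands. At an assumed 10% risk, zero fractures would be rare (1.5%).
- **The longevity claim is one sentence in an abstract.** This is true, and longevity is not a defined endpoint. The sentence still promises something that the design does not observe.

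A reader might also infer three stronger points that the article does not support:

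- That the 6 months in Objectives {7} contradict the 3 months per splint. Two periods of 3 months make 6 months per participant, which agrees with the 6-month control named under Adverse event reporting {22}.
- That the main Discussion promises service life. It says "these parameters determine clinical applicability as well as the service life of the splints" as a reason for measuring them, not as a result the trial will deliver.
- That the wear comparison is equally empty. Volume loss over 3 months is a continuous within-person measure on splints from one digital design and can give valid early evidence.

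**Conclusion.** The point holds for fracture and for the longevity sentence in the abstract. As written, the rule for fracture is either met by any data (0/1 coding) or, in percentage points, met with zero variance when neither type breaks. In the second case the exact upper limit for printed splints is still 8.8% per 3 months, or about 31% per year under a constant hazard. The trial can rule out gross early failure and no more. The 8.8% assumes all 40 participants complete both periods; dropout would widen it. The annual figure rests on the constant-hazard assumption, and how likely a trial without fractures is depends on rates the article does not state. The primary OHIP-G14 analysis and the 3-month wear comparison as early evidence are not called into question by this point.

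**What to change.** - **Statistical methods {20a}:** remove splint fracture rates from the outcomes to which the non-inferiority rule is extended. Report fractures as counts with exact 95% limits for each splint type.
- **Abstract, Discussion:** replace the longevity promise with early (3-month) technical outcome, and state that no conclusion on longevity will be drawn.
- **Objectives {7}, optional:** write 3 months per splint, 6 months in total. The present figure is correct; this only prevents misreading.
- **Main Discussion:** the service-life sentence needs no correction.

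The cost is a change of wording and of one analysis rule, with no added visits, participants or data collection. The downside is that the stated reach of the technical conclusion becomes narrower.

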**Trial registration:**

German Clinical Trials Register (DRKS) DRKS00033904. Registered on March 15, 2024.

## Introduction

### Background and rationale {6a}

Bruxism and temporomandibular disorders (TMD) are common complaints for which patients consult their dentist, with prevalence rates in the adult population exceeding 30% and 5%, respectively [1–3]. The term bruxism refers to an “oromotor behavior” defined as “repetitive jaw-muscle activity characterized by clenching or grinding of the teeth and/or by bracing or thrusting of the mandible.” [4–8]. Bruxism becomes clinically relevant when it leads to destructive teeth wear, failure of dental restorations, teeth, and/or implants and when hypertrophied masticatory muscles impair facial esthetics [6, 9]. Further, bruxism was described as one factor that can contribute to TMD genesis [6]. TMD represents a heterogeneous group of disorders involving the temporomandibular joints (TMJ) and/or jaw muscles with symptoms including TMJ sounds, TMJ and/or jaw muscle pain, and restriction, deviation, or deflection of the mouth opening path [10, 11]. After chronic low back pain, TMD are the second most common musculoskeletal disorder causing pain and disability, with an annual cost of $4 billion in the US [12].

For the management of bruxism and pain-related TMD—referring to myalgia, myofascial pain or arthralgia of the jaw muscles and TMJ(s)—stabilization splints, also known as Michigan-type splints, are employed [6, 13]. These splints are characterized by the following features: they are made from hard acrylic resin, they cover all teeth in the splint-bearing jaw, the posterior teeth of the opposing jaw have even and simultaneous contact with the splint with a flat surface and cuspid rise during splint-guided laterotrusion and protrusion starts after up to 1 mm freedom in centric [14–16]. The therapeutic rationale for stabilization splint usage in individuals with bruxism is the prevention or limitation of dental damage possibly caused by the disorder [6]. Wearing a stabilization splint further results in a change of the functional muscular patterns due to an increase in vertical distance between the upper and lower jaw leading to altered load distribution in the TMJ and jaw muscles [13, 15, 17]. This relieves overstressed areas of these structures and alleviates pain [13, 15, 17].

Nowadays, stabilization splints can be fabricated in a digital workflow, during which they are virtually designed based on a digital impression of the jaws before they are fabricated using computer-aided manufacturing (CAM). The digital workflow is more time efficient and leads to a better fit and patient comfort than the conventional workflow comprising alginate/silicone impressions, cast fabrication, wax-up, and molding the splint from powder-liquid mixtures of polymethylmethacrylate (PMMA) [18–20]. CAM is usually a subtractive procedure during which the splint is milled from an industrially manufactured PMMA blank. From these blanks, 25–30 wt.% are milled away during splint fabrication, 70–75 wt.% remain unused around the splint and are subsequently discarded while the splint itself only accounts for 2–5 wt.% of the blank. Additionally, burs used for milling require frequent exchange since they deteriorate rapidly. Milling, therefore, requires an enormous amount of material and is hence neither cost nor material efficient and has a negative impact on the environment. In recent years, 3D printing has become increasingly popular for splint fabrication. The term “3D printing” is the most commonly used umbrella term in biomedical research for processes in which objects are built additively layer by layer based on a digital file [21, 22]. 3D printing enables the production of more complex geometries with better resource, cost, and time efficiency in comparison to the established milling process. The reason for this is that the ratio of the feedstock material to the material of the final object is higher compared to milling. Furthermore, a parallel production of objects is possible [23–25]. 3D printed stabilization splints may therefore reduce the economic burden and ecological implications of bruxism and TMD management with milled splints. However, the precondition for the production-specific advantages of 3D printing to unfold is that 3D printed splints are not clinically inferior to milled splints. Key clinical outcome parameters for a successful splint therapy are (i) patients' oral health-related quality of life (OHRQoL) with the splints, (ii) therapeutic efficacy, i.e., abrasion of the opposing dentition and pain reduction, and (iii) technical outcome, i.e., fit, wear and fracture rate of 3D printed splints. Due to the unavailability of data on these parameters for 3D printed splints, it is at present not possible to assess a potential inferiority of 3D printed stabilization splints compared to milled stabilization splints.

### Objectives {7}

Therefore, the objective of this clinical trial is to analyze whether the clinical outcome of 3D printed stabilization splints is inferior compared to milled stabilization splints in terms of patients´ OHRQoL and satisfaction with the splints, therapeutic efficacy, and technical outcome. These parameters will be investigated in both—a cohort comprising participants with bruxism and a cohort with participants suffering from pain-related TMD—over a period of 6 months. The null hypothesis states that novel 3D printed stabilization splints for use in bruxism or TMJ and/or jaw muscle pain are not inferior to milled stabilization splints with regard to the aforementioned parameters.

### Trial design {8}

The clinical trial to assess the non-inferiority of 3D printed stabilization splints compared to milled stabilization splints is designed as a monocentric prospective randomized single-blinded crossover trial with two cohorts. According to the indication spectrum of stabilization splints, one cohort comprises 20 participants with bruxism whereas the other arm is formed by 20 participants with pain-related TMD. Only CE-labeled materials are used within their intended purpose for the fabrication of milled and 3D printed splints. In both cohorts, the treatment sequence, meaning that participants either receive a milled splint first and then a 3D printed splint or vice versa is randomized and allocated at a ratio of 1:1. The 3D printed and milled stabilization splints are each worn for 3 months in an order that is blinded to the participants.

## Methods: participants, interventions, and outcomes

### Study setting {9}

The clinical trial is performed at the Department of Prosthetic Dentistry, Center for Dental Medicine, Medical Center, University of Freiburg, Germany.

### Eligibility criteria {10}

For both cohorts, only patients who are being treated at the above-mentioned Department of Prosthetic Dentistry, who are older than 18 years, and who do not require special protection for other reasons are eligible. Treatment with a Michigan-type stabilization splint for the upper jaw to be worn at night is indicated to relieve symptoms of bruxism or TMD. The patient’s state of health must permit dental treatment and patients must have good knowledge of spoken and written German. Patients are only included in the trial if they give written informed consent. General exclusion criteria are known allergies to materials used in the study and drug or alcohol abuse.

Further inclusion and exclusion criteria are specified for the two cohorts as follows:

Bruxism cohort:
Inclusion criteria: The bruxism screening index (BSI) of the German Society of Craniomandibular Function and Disorders (DGFDT) must hint at a probable bruxism.Exclusion criteria: Patients presenting with chief compliant orofacial pain and diagnosed with myalgia or myofascial pain of the jaw muscles and/or arthralgia of the TMJ(s) according to the Diagnostic Criteria for Temporomandibular Disorders (DC/TMD) are excluded from this cohort. Additionally, patients are excluded if they underwent therapies for bruxism that could interfere with the splint treatment, including the insertion of a splint in the month preceding the trial or injections of botulinum toxin into the jaw muscles in the 6 months preceding the trial.TMD cohort:
Inclusion criteria: The patients seek medical treatment because of pain located in the TMJ and/or jaw muscles. Patients are included in the clinical trial if a myalgia or myofascial pain of the jaw muscles and/or arthralgia of the temporomandibular joint(s) according to the DC/TMD are diagnosed and if the Graded Chronic Pain Scale version 2.0 (GCPS) adopts a maximum of grade II.Exclusion criteria: Patients with GCPS grade III or IV are excluded from the clinical trial. Furthermore, patients with orofacial pain of dental, traumatic, or systemic origin requiring medical treatment other than or prior to splint therapy are excluded. In addition, patients are excluded if they received treatment for TMD that could potentially affect the outcome of the splint treatment, such as insertion of a splint in the month prior to the trial, or injections of botulinum toxin into the jaw muscles in the 6 months prior to the trial. TMJ(s) should not show any pain on traction.

The patients of the TMD cohort are diagnosed and treated by dentists who have more than 7 years of clinical experience in the field of prosthetic dentistry and TMD and who have attended structured postgraduate programs in TMD. The dentists were trained and calibrated in the clinical application of the DC/TMD by gold standard examiners in a course of the INfORM Training and Reliability center, University of Leipzig, Germany. The bruxism cohort is treated by a doctorate candidate in dentistry who is supervised by a dentist from the TMD cohort.

